### Treatment allocation, randomization, and blinding

Participants who consent to the study will be randomized in a 5:3 fashion into two open-label arms: group A (treatment arm) or group B (no-treatment arm). The allocation sequence will be generated in advance by a statistician. Upon obtaining informed consent, study personnel will log into the web-based program to determine the participant’s treatment assignment.

While the participant and the treating physician will not be blinded, the laboratory personnel performing the biochemical and morphological evaluations will be blinded ensuring unbiased evaluation. Study outcomes such as birth weight and gestational age are also objective measures.

### Participant timeline and monitoring

Every participant will be screened and enrolment will occur between GW16 to GW24. The rationale for this study initiation range is threefold: (1) it enables us to capture a larger group of eligible women, (2) it permits progesterone exposure during the time period where most fetal growth occurs (late second and third trimesters), and (3) it omits progesterone exposure during the first trimester where increased risk for hypospadias has been reported [49]. Participants will be followed monthly during their pregnancy, at delivery, and until their exit visit at 4 to 8 weeks post-delivery. During this time, information will be collected from participants’ routine blood work, urine sampling, and prenatal ultrasounds conducted as per standard of care.

During the screening visit, the study is introduced and consent is sought if the woman meets study inclusion and exclusion criteria. A screening log is kept, and the demographics of eligible participants who do not consent to the study are collected. Study personnel collect information on the reasons why a potential participant may have declined participation. Eligible women at less than 16 weeks gestation are screened, but consent and enrollment are deferred to GW16.

For the baseline visit, women undergo a full physical examination. Additional blood and urine samples are collected for assessing progesterone levels and meeting exploratory objectives (i.e., analyzing PI drug concentrations, sex steroids, angiogenic, vasoactive, and inflammatory factors and factors associated with placentation, placenta dysfunction, preterm delivery, and fetal growth restriction). Similar blood and urine sample collection occurs at 1 week after the baseline visit, at GW25–GW28, and at GW33–GW36. During the baseline visit, demographics and relevant medical history are collected by chart review and from the participant as required. Participants are then randomized into either group A or group B. After being appropriately educated on how to self-administer progesterone capsules intravaginally, participants in group A begin progesterone supplementation (administered as two capsules of Prometrium 100 mg) nightly from GW16–GW24 until GW36.

Follow-up visits occur monthly for both study groups. Participants undergo a targeted clinical evaluation. Assessment of safety includes clinical observation and monitoring of laboratory measurements. Symptoms, physical exam findings, and laboratory findings are graded based on the DAIDS Table [48]. At each monthly visit, all participants complete a questionnaire to report any adverse events they may have experienced in the past month. For group A, study medication compliance is assessed at each monthly visit through a capsule count. A compliance questionnaire captures how frequently group A participants have been taking the progesterone and a second adherence questionnaire is provided if participants miss dose(s) to record the reason(s) they missed their medication. If any of the participants miss a follow-up visit, a questionnaire records reasons why they missed their appointment.

At delivery, a clinical and laboratory evaluation of the infant (e.g., birth weight, gestational age at birth, sex, umbilical cord gas results, and Apgar score) is performed according to standard of care. Maternal blood, cord blood, placenta, umbilical cord, and membrane tissue samples are also collected to meet exploratory objectives.

An exit visit occurs 4–8 weeks post-delivery. During this visit, participants undergo a targeted clinical evaluation and complete a short exit questionnaire that allows participants to reflect on their involvement in the study and provide suggestions for the study moving forward with a larger RCT.

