### Data recording and adverse event reporting

Data recording will occur using a study case report form (CRF). Data from the CRF will be consolidated into a secure, password-protected internet-enabled database with built-in quality checks.

Any AE that occurs between the time a study participant signs the informed consent form and the time she departs the study at the end of the final follow-up visit (or at the time of early discontinuation from the study for any reason) will be captured and recorded. The start date, the stop date, the severity of each reportable event, and the judgment of the AE’s relationship to the study medication/intervention will also be recorded. All serious adverse events (SAEs) occurring during the course of the study will be reported to the project manager within 24 h of the site becoming aware of the event. Adverse events that had previously been reported by the study subject will also be reassessed for duration, intensity, and possible reoccurrence. All AEs and SAEs will be followed until resolution or until the investigator and the clinical/medical monitor are in agreement that the AE/SAE has stabilized and no more follow-up is required. If an SAE is ongoing at the time a participant discontinues/completes the study, the SAE will be followed until the investigator agrees that the event is satisfactorily resolved, becomes chronic, or that no further follow-up is required.

A Data and Safety Monitoring Board (DSMB) will review the AE/SAE reports submitted by the sponsor/central study coordinator. The DSMB might conclude the study early if unacceptably high rate of AE/SAE is observed.

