### Statistical analysis

The primary endpoint is the proportion of enrolled participants out of all eligible patients. Qualitative information on the reasons to decline participation will be collected and summarized.

Secondary endpoints include the safety of progesterone supplementation during pregnancy for HIV-positive women as measured by the frequency and severity of AEs in group A and group B. Compliance to progesterone supplementation will be assessed in group A by the proportion of missed doses out of the total prescribed doses per participant. The acceptability of the intervention and barriers to adherence to progesterone supplementation will be recorded for participants in group A. For both group A and B participants, barriers to appointment attendance will be captured and acceptability of the entire study will be assessed in an exit questionnaire.

The relationships between progesterone levels (serum or urine) at baseline, 1 week post-baseline, GW25–GW28 or GW33–GW36 and birth weight, birth weight percentile, and gestational age at birth will be assessed with Spearman’s rank correlation. Serum/urine progesterone levels will be compared between women with and without an AE/SAE using descriptive statistics, if sufficient numbers of events occur. The levels of biomarkers will be compared between the two arms at baseline, 1 week post-baseline, GW25–GW28, GW33–GW36 and delivery visits using descriptive statistics and graphical methods. Qualitative assessment of placenta morphology will be performed blinded to the arm allocation and birth outcome.

Although, this pilot study is not powered for subgroup analyses, qualitative assessment of the impact of race, age, previous adverse pregnancy outcome on enrollment into study, acceptability of progesterone, and adherence will be conducted where possible.

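### The adverse-event questionnaire looks back only one month, so a missed visit or a late exit visit leaves time that no questionnaire asks about, and mild self-reported events may be lost

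*Protocol article*

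**What the plan says.** All references are to the Protocol article.

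- Participant timeline and monitoring sets the schedule: "Participants will be followed monthly during their pregnancy, at delivery, and until their exit visit at 4 to 8 weeks post-delivery". It adds "Follow-up visits occur monthly for both study groups", and for AEs "At each monthly visit, all participants complete a questionnaire to report any adverse events they may have experienced in the past month".
- For absences the same section says: "If any of the participants miss a follow-up visit, a questionnaire records reasons why they missed their appointment". It describes no AE catch-up question.
- The exit visit consists of a targeted clinical evaluation and a short questionnaire on the woman's experience of the study. No AE form is named there or at delivery.
- Data recording and adverse event reporting sets the obligation. What must be recorded, with start and stop dates, is "Any AE that occurs between the time a study participant signs the informed consent form and the time she departs the study". Departure there means her last visit, or the point at which she discontinues if that comes sooner.
- Outcomes says that safety is assessed through questionnaires and AE recording, and that the arms are compared on the proportion of participants who report AEs. Statistical analysis describes safety "as measured by the frequency and severity of AEs in group A and group B".

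**The concern.** The article chose to state the recall period, so this is not a detail merely left to a fuller document. A fixed one-month window gives unbroken coverage only if each completed questionnaire follows the previous one within a month. The protocol's own arrangements can break that in two ways. It expects missed visits, since it collects the reasons for them and treats barriers to attendance as something to measure. It also allows exit as late as 8 weeks after delivery.

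Preliminary safety and tolerability information is a stated secondary objective. The events at risk are mild, short-lived symptoms such as headache or nausea, which are known mainly because the woman reports them. A woman whose only AE fell in unasked time, and was not found another way, is counted among those without an AE.

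**Working it through.** The plan gives no figure for AE coverage, so there is nothing to reproduce. The check is coverage arithmetic for the questionnaire alone. One month is taken as 4.0 weeks or 30.4375/7 = 4.35 weeks.

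**1. One missed monthly visit**

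Unasked time = interval between completed forms − recall = 2 months − 1 month = 1 month, or 4.0 to 4.35 weeks.

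Treatment runs from entry at gestational week (GW) 16–24 to GW36:
- Entry at GW16: 36 − 16 = 20 weeks. Share unasked 4.0/20 = 20% to 4.35/20 = 22%.
- Entry at GW24: 36 − 24 = 12 weeks. Share unasked 4.0/12 = 33% to 4.35/12 = 36%.

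For total follow-up, delivery at GW37–40 is my assumption. The shortest is 37 − 24 + 4 = 17 weeks and the longest is 40 − 16 + 8 = 32 weeks. The unasked share lies between 4.0/32 = 12.5% and 4.35/17 = 26%.

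**2. Delivery to exit**

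Suppose, favourably, that the AE form is completed at both delivery and exit. Unasked time = max(0, exit week − recall).
- Exit at 4 weeks: 0.
- Exit at 6 weeks: 6 − 4.35 = 1.65 to 6 − 4.0 = 2.0 weeks (28–33% of the interval).
- Exit at 8 weeks: 8 − 4.35 = 3.65 to 8 − 4.0 = 4.0 weeks (46–50%).

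Assume exit is uniform over 4–8 weeks and recall is 4.35 weeks. The mean unasked time is then (8 − 4.35)²/(2 × 4) = 1.67 weeks. With mean entry at GW20 and delivery at GW40, mean follow-up is 40 − 20 + 6 = 26 weeks, so the share is 1.67/26 = 6.4%. If no AE form is given at exit, the questionnaire asks about none of the time after the last completed form.

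**3. Effect on the proportion reporting an AE (illustration only)**

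Let P be the true proportion with at least one AE, u the share of time unasked, and c the share of events in that time found by other channels. With a constant event rate and brief events, observed proportion = 1 − exp[−λ(1 − u + uc)], where λ = −ln(1 − P). None of P, u or c is given in the document. Take P = 50% and u = 15–30% for every woman:
- c = 0: 44.5% to 38.4%.
- c = 0.5: 47.3% to 44.5%.
- c = 1: 50%, no loss.

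This overstates the loss in two respects. Only women with a gap are affected, so the loss shrinks in proportion to their share. An event lasting into the recalled month would still be reported with its start date.

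**4. Can other channels fill the gap?**

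Clinical observation, the targeted evaluation and laboratory monitoring are described as part of follow-up visits, so a missed visit can lose them too. A later examination need not reveal a resolved symptom. The 24-hour report covers serious events only. The reassessment rule covers only AEs already reported. The capture obligation says what must be recorded, not how the event comes to light.

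**The case against.** The strongest reply is that the questionnaire is one AE source among several. The article requires every AE to be captured with dates and provides for clinical evaluation, including at exit. It also has separate standardized questions on local irritation for group A. With monthly visits, one month is a natural description of the visit interval, and the exact prompts may sit in the case report form. Progesterone stops at GW36, so the post-delivery gap falls after treatment, and with exit at 4 weeks and forms at delivery and exit there is none. All of this stands and keeps the point small. It does not remove it, because the stated window still leaves a mild, resolved event in the unasked month without a described route to the record.

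A reader might go further and infer that unobserved time is counted as event-free and that the AE rate ratio between arms is biased. The document does not support that. No person-time rate is planned, the Statistical analysis section states no period for AE frequency, and nowhere is unobserved time treated as event-free. The schedule and the form are the same in both arms, so a between-arm bias would need differential attendance, which nothing here shows. Even then, with 25 and 15 women and an assumed 50% AE proportion in each arm, the standard error of the log risk ratio is √(0.5/12.5 + 0.5/7.5) = 0.327. The 95% interval around a ratio of 1 is about 0.53 to 1.90, so a modest shift would not be visible.

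A reader might also infer that the decision on a larger trial is at risk. The safety criterion for that decision is a grade 4 or serious event attributed to progesterone, which missed mild symptoms hardly touch.

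**Conclusion.** The point holds in a limited form and is minor. The stated one-month recall does not by itself meet the consent-to-exit capture obligation. Each isolated missed visit leaves about 4 of the 12 to 20 treatment weeks unasked. An exit visit later than about 4 weeks after delivery leaves up to about 4 further weeks, or more if no AE form is used at exit. The proportion of participants who report AEs may therefore be somewhat low. By how much is unknown: it depends on how many visits are missed, how long events last and how much other channels recover, none of which the document gives. The finding concerns completeness of AE capture. It does not show a bias between arms or an error in the planned analysis. If the case report form already asks about the time since the last visit, only the article's wording needs correcting.

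**What to change.** In Participant timeline and monitoring, change the recall period of the AE questionnaire to *since the last completed study visit (or since consent, for the first)*, and state that the same form is given at the exit visit. The recall intervals then join up over the period in Data recording and adverse event reporting, whatever the attendance pattern before exit. Keep the proportion of participants reporting AEs as the analysed measure; a denominator of covered time is not needed.

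The cost is a wording change and one existing form at an existing visit. The downside is a longer recall after a missed visit and at exit, so dates and grades of mild events will be less exact.

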### Early termination

Participation in the study will be terminated early if: the participant refuses further treatment and/or follow-up evaluations; the study staff or participant’s medical provider determines that further participation in the study would be detrimental to the participant’s or her fetus’ health or well-being; the participant is non-compliant with the study requirements in a manner that is either detrimental to her health or interferes with the validity of the study results; or the sponsor terminates the study.

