### Outcomes

The primary outcome is feasibility. The proportion of HIV-positive, pregnant women who are approached and screened but do not meet eligibility criteria will be recorded, as well as the proportion of women who meet eligibility criteria but decline to participate. Data will be collected on the gestational age at screening and enrollment. Data will also be collected on the reasons for non-participation. This information will be used to determine the number of centers that will be required for timely recruitment of a larger randomized control trial (RCT). A consent rate of less than 60 % among women that meet eligibility criteria would be grounds for not moving forward with a larger RCT in this setting.

Secondary outcomes include safety, acceptability, compliance, and barriers to adherence. Safety and tolerability will be assessed through questionnaires administered to participants during the study, and by recording adverse events (AE) using the Division of AIDS (DAIDS) Table for Grading the Severity of Adult and Pediatric AEs and Addendum 1 Female Genital Grading Table for Use in Microbicide Studies [48]. AEs of all grades will be recorded, and the proportion of participants who report AEs will be compared between study arms. Any grade 4 AE or severe adverse event (SAE) attributed to progesterone supplementation would be grounds for not moving forward with a larger RCT. Standardized questions will capture group A’s experience with progesterone self-administration and information on local irritation or discomfort. Study acceptability will be measured by capturing whether participants are willing to be randomized to the no intervention arm, and participants’ overall impression of the study. Compliance to treatment will be assessed in group A via capsule count and through a standardized compliance questionnaire at each follow-up visit. Barriers to adherence to progesterone supplementation, and to study follow-up visits, will be assessed using standardized questionnaires.

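### The early-termination rule ends study follow-up, not only capsule use, when a woman refuses treatment or is judged too non-compliant, so the secondary outcomes are truncated selectively

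*Protocol article*

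**What the plan says.** In the protocol article, Early termination lists the events that end participation in the study. One is that "the participant refuses further treatment and/or follow-up evaluations". The joining words mean that refusing treatment is enough, even if the woman would still attend visits. Another is that "the participant is non-compliant with the study requirements in a manner that is either detrimental to her health or interferes with the validity"; the validity meant is that of the trial's findings, and no threshold is given for this limb.

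Under Outcomes, the same behaviour is something to be measured: "Secondary outcomes include safety, acceptability, compliance, and barriers to adherence". Statistical analysis defines compliance in group A as "the proportion of missed doses out of the total prescribed doses per participant".

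On data collection:
- **Compliance.** Participant timeline and monitoring says that for group A "study medication compliance is assessed at each monthly visit through a capsule count", with questionnaires on how often capsules were taken and why doses were missed.
- **Adverse events.** Data recording and adverse event reporting starts capture at consent and closes it at the final follow-up visit ("or at the time of early discontinuation from the study for any reason) will be captured and recorded"). Events already reported are followed to resolution or stabilisation.
- **Acceptability of the whole study.** Statistical analysis takes this from an exit questionnaire. Participant timeline and monitoring places it at a visit 4 to 8 weeks after delivery, where "participants undergo a targeted clinical evaluation and complete a short exit questionnaire". No version for women who leave early is described.

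**The concern.** In this pilot, refusing capsules and missing doses are results. A rule that answers them by ending participation closes observation on the women who carry most of the information about tolerability, adherence and acceptability. The loss depends on the outcome itself, so it is informative. One route to it, refusal of capsules, does not exist in group B, so it is also uneven between arms.

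Four things are at stake:
- the adherence figure handed to the planners of the larger trial;
- the between-arm comparison of the proportion with adverse events, because group A women who stop are observed for less time;
- the whole-study acceptability result, which would come mostly from women who stayed;
- exploratory outcome (c), which relates degree of adherence to birth outcomes and would lose its low-adherence end.

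An analysis plan cannot repair this afterwards, because the data would not have been collected.

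**Working it through.** **The plan's own figures.** 40 women at 5:3 gives 40 × 5/8 = 25 in group A and 40 × 3/8 = 15 in group B, as stated. No compliance, dropout or power figure is stated, so what follows illustrates the mechanism and does not correct a number.

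**What happens to a woman who refuses capsules but would accept visits**

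| Item | Up to termination | After termination |
|---|---|---|
| Capsule counts, compliance and barrier questionnaires | Collected monthly | Not collected |
| Adverse events | Recorded | Existing events followed; new ones not captured |
| Delivery data and samples | Not yet due | Not collected under the rule |
| Exit questionnaire | Not yet due | Not given |

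**Missed doses: inputs**
- From the document: 25 women in group A; nightly dosing from a start between GW16 and GW24 until GW36.
- Assumed: start at GW20, so 16 × 7 = 112 planned nights, all before delivery; women who continue miss 10%; women who stop miss 50% until they are terminated; *k* women are terminated at night *s*.

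**Formulas**
- Counted to termination: [(25 − *k*) × 0.10 + *k* × 0.50] / 25
- Counted to GW36: [(25 − *k*) × 0.10 + *k* × *m*] / 25, where *m* = (0.50 × *s* + 112 − *s*) / 112

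For *s* = 28 nights (4 weeks), *m* = (14 + 84)/112 = 0.875. For *s* = 56 nights (8 weeks), *m* = (28 + 56)/112 = 0.75.

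For *k* = 5:
- to termination: (2.0 + 2.5)/25 = 18.0%
- to GW36, stop at 4 weeks: (2.0 + 4.375)/25 = 25.5%
- to GW36, stop at 8 weeks: (2.0 + 3.75)/25 = 23.0%

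| Terminated, of 25 | To termination | To GW36, stop at 4 weeks | To GW36, stop at 8 weeks |
|---|---|---|---|
| 2 | 13.2% | 16.2% | 15.2% |
| 5 | 18.0% | 25.5% | 23.0% |
| 8 | 22.8% | 34.8% | 30.8% |

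**Exit questionnaire, group A only.** Assume that 90% of women who reach it are favourable, and that 0% to 20% of terminated women would have been. With 5 terminated, the questionnaire reads 90%. Among all 25 the figure would be (0.90 × 20 + 0 × 5)/25 = 72% to (0.90 × 20 + 0.20 × 5)/25 = 76%.

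**The case against.** The strongest reply is that little is lost and that the rest belongs in a fuller document. Much of this is right.

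- A reader might infer that terminated women are dropped from the compliance, tolerability and acceptability outcomes. The article does not say so. Their monthly data exist, and nothing excludes them from analysis. An illustration in which they vanish (missed doses reading 10% in the example) models something the article does not state.
- Ordinary missed doses do not trigger termination. The article expects them and provides a questionnaire for them. Only non-compliance that harms health or threatens validity counts, it covers study requirements in general, and it applies to both arms.
- Acceptability is not measured only at exit. Group A's experience of self-administration and every woman's willingness to be randomised to no intervention are captured separately. Only the overall exit assessment is tied to the post-delivery visit.
- A reader might infer that a randomised comparison of birth outcomes is compromised. None is specified: the article plans distributions, correlations and the relation with adherence. The specified between-arm comparisons are of adverse events and, descriptively, biomarkers.
- Adverse events while a woman is taking capsules and still in the study are captured; what goes missing is later-emerging events.
- How the dose denominator treats a woman who stops could be left to an analysis plan.

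What remains is that the rule is stated, not omitted. As written, refusing capsules alone ends participation, and new adverse events are then no longer captured. A fuller analysis plan can define a denominator, but it cannot supply a delivery record or an exit questionnaire that was never obtained.

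**Conclusion.** The point holds as one of selective truncation. The rule treats stopping capsules, or capsule non-compliance thought to affect validity, as leaving the study. It therefore cuts short the safety, adherence and whole-study acceptability data of the women least favourable to the intervention, with one route open only in group A. The likely direction favours progesterone.

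The size cannot be known in advance. Under the stated assumptions, 5 terminations among 25 women understate missed doses by 5.0 points (23.0 − 18.0) to 7.5 points (25.5 − 18.0), even when all data to termination are used. With 2 terminations the gap is 2.0 to 3.0 points, and with 8 it is 8.0 to 12.0 points. These figures rest on the assumed start week, missed-dose rates and time of stopping.

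The primary endpoint, enrolled out of eligible, is settled at enrolment and is unaffected, as is the 60% consent criterion. A reader should not infer that the feasibility conclusion is at risk. When treatment should stop is a clinical matter on which this point takes no position.

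**What to change.** In Early termination, distinguish two events: discontinuing study capsules and withdrawing from the study. State that refusal of capsules, or capsule non-compliance said to affect validity, does not by itself end outcome follow-up. Leave the health-related grounds for termination unchanged.

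Then bring the other sections into line:
1. Unless the woman declines follow-up or withdraws consent, continue adverse-event capture, monthly questionnaires, delivery data and the exit visit.
2. Offer the exit questionnaire at the time of any early withdrawal.
3. Report compliance against the nights planned from first dose to the earlier of GW36 or delivery, with nights after stopping counted as missed. Report compliance while on treatment alongside it.
4. Keep every woman in her assigned arm in the between-arm summaries.

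The cost is protocol wording, a few visits that are already on the schedule for women who have stopped capsules, and possibly a less favourable compliance figure. The change only helps women whose follow-up has not yet been ended, so it should be made before enrolment or as early in it as possible.
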